## Study dissemination

### Confidentiality

All study-related information will be stored securely at the study site. All participant information will be stored in locked file cabinets in areas with limited access. All laboratory specimens, reports, data collection, process, and administrative forms will be identified by a coded ID (identification) number only to maintain participant confidentiality. All records that contain names or other personal identifiers, such as locator forms and Informed Consent Forms, will be stored separately from study records identified by code number. All local databases will be secured with password-protected access systems. Forms, lists, logbooks, appointment books, and any other listings that link participant ID numbers to other identifying information will be stored in a separate, locked file in an area with limited access. Participants’ study information will not be released outside of the study without the written permission of the participant.

### Access to data

The Data Management Coordinating Center will oversee the intrastudy data sharing process. All data sets will be password-protected. The principal investigator will have direct access to the data sets. With her permission, the statistician will utilize the data sets for analyses. Requests from outside for further research cooperation will be discussed by the Steering Committee. The research protocol will be published. There is no plan for granting public access to the full participant-level data sets.

### Publication policy

All publications should be conducted and monitored by the principal investigator and the Steering Committee. That means that each paper or abstract must be written, reviewed, released, and published with the authorization of the PI and the Steering Committee. The timing of presentation of the endpoint data and the meetings at which they may be presented will also be determined by PI and the Steering Committee.

In order to achieve the study objectives and maintain scientific integrity, data should be analyzed collectively; a participating site is not permitted to publish its data and analysis results independently. If there are some invitations from workshops, symposia, and volumes in related area, individuals who work on such requests should report to the PI and Steering Committee with a detailed proposal, and state clearly what to present and how to present.

### Authorship eligibility

Many topics will be suggested based on the study database, and each topic might be possible to be developed into a peer-reviewed article. The PI and the Steering Committee will work together to decide the authorship of each article, on basis of contributions to the manuscripts; the investigator who contributes most will be considered as the first author. Disputes regarding authorship will be resolved by the PI with careful considerations. If professional writers are needed, the PI and the Steering Committee will determine whether to include them in authorship.

## Discussion

The current conventional treatment on hyperlipidemia, statins, not only can entail significant cost to patients and society, but also is associated with low treatment compliance and high rates of side effects [3, 4]. Effective treatment alternatives on hyperlipidemia have been explored to address the shortcomings of statins; and acupuncture and moxibustion are considered as potentially effective regimens based on clinical practices and clinical research [9–11, 17, 18, 23]. However, acupuncture and moxibustion, separately, have not been proved to be as effective as statin from previous studies, despite the existence of their clinical effects [9–11, 17, 18, 23]. Additionally, as approaches of complementary and alternative medicine (CAM), their introduction to the mainstream medical community is often limited due to lack of robust evidence and differences in the philosophy adopted. Therefore, the RCT described in this paper has been developed to validate the efficacy and safety of combined acupuncture and moxibustion on hyperlipidemia via a well-designed evaluation.

There are several strengths in design of this study. First, the intervention adopted in this study is developed not only based on profound TCM theory but also supported by comprehensive scientific research. The theory guiding the acupoints selection and traditional Chinese herb composition has been studied, identified and well-demonstrated in this study which is discussed in the “Treatment rationale” section. Meanwhile, several studies from the perspectives of laboratory animal medicine and clinical medicine have been conducted [9–11, 17, 18, 23] which serve as the key foundation of intervention development in this study. Specifically, the biological mechanism was explored on how cake-separated moxibustion can have an impact upon hyperlipidemia; and the acupoint selection and regimen implementation from ample TCM theory were validated in multiple clinical studies.

Second, the TLC will be included prior to both interventions of acupuncture and moxibustion and statins, which enables this study to reflect the actual practice in clinical settings to the greatest extent. According to the guideline of hyperlipidemia treatment [20], TLC is recommended as the first step before any other treatment. By adhering to the commonly adopted clinical guideline during study procedure, on the one hand, we can take good care of the “non-maleficence” and “justice” principles in study ethics, because the opportunity of receiving appropriate medication will not be compromised for patients attending this study; on the other hand, this can enhance the generalizability of this study due to following the clinical operations in real life.

Third, the stratification on risk levels for heart disease [19, 20] will be applied to this study, which makes possible that the effect of interventions of this study can be differentiated and specified according to different risk groups. Patients with hyperlipidemia may enter the study with different initial lipid levels, due to different time points of initiating medication intervention for groups with different risk levels. Meanwhile, the goal lipid level for each patient may also differ accordingly. It is impractical and erroneous to set exactly the same criteria in determining the clinical effect for all the patients. In recognition on this, patients will be stratified by their risk levels during the study, and then the effects of acupuncture and moxibustion versus simvastatin can be observed and examined within different risk levels, instead of within a large group with extensive variance. This stratification reflects that patient’s risk levels for heart diseases are considered important impacting factors on the outcomes in this study; it enables exploring this impact upon the effects of interventions, which can further guide the appropriate intervention by targeting on the right populations. In addition, different treatment goals will be adopted for different risk groups according to the standard clinical guideline; this ensures the study will be implemented in accordance with the daily clinical practices to the most extent, thus, the external validity can be mostly warranted.

However, certain limitations still exist in this study. One is the absence of a placebo control group due to the limited study budgets. Because of this lack of comparison, it may not be able to determine whether the outcome observed is due to the therapeutic effect of acupuncture and moxibustion or its placebo effect, if acupuncture and moxibustion is proved to be inferior to simvastatin. Nevertheless, judgment from clinical experiences and relevant findings from previous studies can help in identifying and justifying the effect with clinical significance.

Another limitation is the absence of blinding in patients and health care providers due to the operation characteristics of acupuncture and moxibustion. With patients knowing their intervention assignments after randomization, there may be a potentially higher possibility of cross-over between and drop-off from these two arms; thus, the potential selection bias may occur. But detailed explanation can be given to patients on these two arms of interventions in order to inform potential effects and safety in both arms. This will help limiting the drop-off and cross-over rates. Moreover, with the intervention assignment revealed, the effect identified from the acupuncture and moxibustion group may not fully result from its therapeutic aspect but a psychological aspect. But the outcome measures examined in this study are all objective – based on the fasting lipid level; and in the analysis process intervention assignment is fully blinding to data assessors. Therefore, the information bias due to lack of blinding could be controlled to a considerable extent.

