In general, acupuncture and moxibustion is shown to be possibly effective in treating hyperlipidemia, with lower cost and fewer serious adverse events [17, 18]. However, due to the lack of robust study design and assessment methodology in existing clinical studies, the findings should be interpreted with caution. According to previous attempts on identifying an optimal regimen of acupuncture and moxibustion for treating hyperlipidemia, the warm needling acupuncture along with medicinal cake-separated moxibustion seems to be a modality that successfully combines the advantages of both acupuncture and moxibustion. This is worth further exploring to warrant its therapeutic effects [12, 15, 16]. So far, very few studies on this combined intervention are available. Hence, there is a need for a well-designed randomized control trial to validate the efficacy and safety of warm-needling acupuncture along with medicinal cake-separated moxibustion, by comparing it with statins.

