### Trial design

This is a multicenter, open-label, randomized, stratified, active-controlled, noninferiority trial with two parallel groups. Randomization will be performed with a 1:1 allocation. Subjects with LDL-C values above the recommended level who meet the inclusion/exclusion criteria will be stratified based on their risk levels of heart disease [19, 20]. Then, they were instructed to follow the NCEP Adult Treatment Panel (ATP) [20] Therapeutic Lifestyle Change (TLC) diet first. After TLC is completed, subjects who have not reached the target lipid level will be randomly assigned to the treatments of either acupuncture and moxibustion or simvastatin. The duration of treatment for this study will be 12 weeks, followed by another 4 weeks for post-treatment assessment.

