**Fig. 2 Fig2:**
[figure not shown]
Treatment regimen flowchart. This figure demonstrates the treatment regimen and flowchart for intervention of warm needling and medicinal cake-separated moxibustionSimvastatinDosage: simvastatin (10 mg/day)AdministrationAll simvastatin tablets will be stored in the central pharmacy and assigned to each investigator site by a qualified staff. The drug will be administered orally to subjects at the investigator site by a physician or a nurse in accordance with instructions in the medication guidesSchedule: 7 days per week for 12 weeksDosage adjustment:there will be no dose adjustments in this study. If, in the opinion of the investigator, a subject is unable to tolerate a specific dose of simvastatin and requires dosage adjustment, that subject will discontinue simvastatin but will continue to return for all other study procedures and measurements until the end of the study

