### Statistical methods

#### Dataset analysis

For the primary endpoint of percentage change in LDL-C from baseline, the efficacy of acupuncture and moxibustion will be evaluated at week 12 by comparing the treatment effect to that of the active control group. A type I error of 0.05 will be allocated to the test.

There are three main analysis sets:Full analysis set (FAS): includes all randomized subjects who have received at least 1 investigational treatmentCompleter Analysis Set (CAS), includes subjects in the FAS who completed their scheduled intervention and have a nonmissing LDL-C value at week 12Effect Durability Analysis Set (EDAS), includes subjects in the FAS who completed their scheduled intervention and have non-missing LDL-C values at week 6 and week 12

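### The no-placebo caveat is tied to an inferior result; it applies at least as strongly to a noninferior one, and efficacy should be read from noninferiority only if the simvastatin response supports it

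*Protocol article*

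**What the plan says.** Trial design describes an "active-controlled, noninferiority trial with two parallel groups". The aim in Background and rationale is to "validate the efficacy and safety of warm-needling acupuncture along with medicinal cake-separated moxibustion, by comparing it with statins", and the opening of the Discussion repeats the aim of validating efficacy. Under Dataset analysis, "the efficacy of acupuncture and moxibustion will be evaluated at week 12 by comparing the treatment effect to that of the active control group".

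The limitations in the Discussion begin with the missing arm: "One is the absence of a placebo control group due to the limited study budgets". The consequence drawn is that the trial may not be able to tell apart the "therapeutic effect of acupuncture and moxibustion or its placebo effect, if acupuncture and moxibustion is proved to be inferior to simvastatin". The mitigation offered is that "judgment from clinical experiences and relevant findings from previous studies can help in identifying and justifying the effect with clinical significance". A second limitation, on lack of blinding, adds that "the effect identified from the acupuncture and moxibustion group may not fully result from its therapeutic aspect but a psychological aspect", without tying this to either result.

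The control is one fixed dose of simvastatin, for which "there will be no dose adjustments in this study". Subjects who cannot tolerate it stop the drug but stay under measurement.

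**The concern.** The caveat is absent where it matters most. If the trial shows a difference, it has at least demonstrated that it can separate two treatments. If it shows similarity, the data fit two opposite explanations: both treatments lowered LDL-C, or neither did. Only evidence that simvastatin worked in this trial can choose between them.

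The article itself makes a weak control arm conceivable:

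- Simvastatin is given at the site every day for 12 weeks (7 × 12 = 84 doses), and the article describes statins as having poor compliance and frequent side effects.
- The primary analysis set keeps everyone who received at least one treatment, so early stoppers remain in it and can dilute the simvastatin effect.
- Subjects are randomized because LDL-C after the diet period is still above goal. If the sample that decides this is also the day-1 baseline, both arms can be expected to fall somewhat without any treatment effect.

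At stake is the headline conclusion. Followed as written, a trial in which simvastatin underperformed could be reported as validating acupuncture and moxibustion, and the stated no-placebo limitation would not attach to that report.

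**Working it through.** **Inputs.** Effect size 0.343 and SD 0.7 on absolute LDL-C change (no unit given), power 0.80 and 65 per group, all from Sample size. Type I error 0.05 from Dataset analysis; two-sided tests from the Statistical analysis plan subsection. The significance level printed as 0.95 is read as alpha 0.05. No noninferiority margin is given anywhere in the article. Reading 0.343 as the margin M is an assumption made here for illustration.

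**Step 1: reproduce the plan's figure.** n per group = 2 × [0.7 × (1.960 + 0.842) / 0.343]² = 65.4, which rounds up to 66. The same formula serves a noninferiority test with M = 0.343, true difference 0 and one-sided 0.025. Power at 65 per group is 79.8%. The stated 65 reproduces.

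**Step 2: chance of declaring noninferiority when acupuncture and moxibustion does nothing.** SE = 0.7 × √(2/65) = 0.1228. With S the true simvastatin reduction, P = Φ((M − S)/SE − 1.96). For S = 0: Φ(0.343/0.1228 − 1.96) = Φ(0.83) = 79.8%.

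| True simvastatin reduction S (M = 0.343) | P(noninferiority declared) |
|---|---|
| 0 | 79.8% |
| 0.1 | 50.8% |
| 0.2 | 21.3% |
| 0.343 | 2.5% |
| 0.5 | 0.06% |

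The test sees only the difference between arms, so two inert treatments pass exactly as often as two equally effective ones. The error falls to its nominal 2.5% only when simvastatin's effect in this trial is as large as the margin.

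**Step 3: vary the assumed margin, both treatments inert (S = 0).** M = 0.1 gives 12.6%, 0.2 gives 37.0%, 0.343 gives 79.8%, and 0.5 gives 98.3%.

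**Step 4: look for a stated use of the control response.** Dataset analysis compares the arms at week 12. The Statistical analysis plan subsection models treatment, visit and their interaction, then repeats the analysis in completers. Consistency analysis compares the treatment effect at week 6 with that at week 12. None requires the simvastatin arm's own change to reach any level or to match an outside effect.

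**Limits of this arithmetic.** It is on the absolute scale, whereas the primary endpoint is percentage change, for which no SD is given. The documents give no within-person variability, so the fall from regression to the mean cannot be sized from them.

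**The case against.** The strongest reply is that the Discussion's sentence is true. After an inferior result, the trial still could not say whether acupuncture and moxibustion beats placebo. This stands: the sentence is incomplete, not wrong.

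A reader might go further and infer that a noninferior result is the only one affected, or that it cannot be interpreted at all. The documents support neither reading. Noninferiority gives indirect evidence of efficacy if simvastatin's effect exceeds a justified margin, and LDL-C on day 1 and at weeks 6 and 12 is collected in both arms.

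Other points reduce the concern:

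- The psychological-effect caveat covers any result, so attribution is partly addressed. It concerns blinding, however, not whether the control worked.
- The diet period comes before randomization and the analysis baseline is taken after it, so the run-in fall is not counted. Only continuing diet change and regression to the mean remain. The article leaves open whether the deciding sample and the day-1 baseline are the same draw.
- Supervised dosing, the adherence outcome, the completer analysis and the goal-attainment rate would make a badly delivered control visible. None is a rule for what may then be concluded.
- The mitigation cites earlier studies as well as judgment. Background and rationale itself asks for caution with the existing clinical studies because their design was not robust.
- A rule on the control response could sit in a full protocol or analysis plan that is not shown. Its absence from the article is therefore not itself the fault. The fault is the printed sentence, read with the printed efficacy aim.

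Finally, a change from baseline within the simvastatin arm is uncontrolled and contains the same artefacts that affect both arms. This is correct and limits what the fix can deliver.

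**Conclusion.** The point holds in this form: the no-placebo caveat should extend to a noninferior result, where it applies at least as strongly, and noninferiority alone should not be read as validated efficacy. The stated comparisons cannot tell two effective arms from two ineffective ones. On the plan's SD and group size, with 0.343 assumed as the margin, two inert treatments would be called noninferior 79.8% of the time. This falls to 2.5% once simvastatin's true effect equals the margin. These figures rest on the assumed margin, on the absolute scale and on acupuncture and moxibustion being inert. They show how strongly the conclusion depends on the control arm; they do not predict that simvastatin will fail. The change should be made because it alters what the trial may conclude.

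**What to change.** 1. Reword the limitation in the Discussion so that the no-placebo caveat covers a noninferior result as well as an inferior one.
2. State the noninferiority margin and the statin effect that justifies it.
3. State that noninferiority will be read as evidence of efficacy only if the simvastatin arm's week-12 percentage change in LDL-C, with its 95% CI from the existing mixed model in both the full and the completer analysis sets, is consistent with that statin effect. Fix the threshold in advance, clearly above the fall expected from regression to the mean and continuing diet change.
4. If the condition is not met, conclude only that acupuncture and moxibustion was no worse than simvastatin as given in this trial.

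The cost is a few sentences and one within-arm estimate from data already planned; no extra visits or subjects are needed. The downsides are that efficacy wording may have to be withheld, and that the check is supportive rather than proof because it is a within-arm change.

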## Conclusion

In conclusion, efforts have been devoted, in this study, to developing a well-designed assessment approach to evaluate the efficacy and safety of combined acupuncture and moxibustion on treating hyperlipidemia, by integrating the TCM regimens with the standardized Western medicine appraisal approach. It is expected this assessment will introduce a potentially effective alternative treatment of hyperlipidemia by borrowing the wisdom from the time-tested practice approach, TCM.

## Trial status

Primary registry and trial identifying number: ClinicalTrials.gov NCT02269046Date of registration in primary registry: 16 October 2014Primary sponsor: The First Affiliated Hospital of Hunan University of Traditional Chinese MedicineContact for public queries: [name]. Email: [contact] for scientific queries: [name]. Email: [contact] title: Acupuncture and Moxibustion for HyperlipidemiaScientific title: Acupuncture and Moxibustion for Hyperlipidemia (AMH-RCT): Study Protocol for a Randomized Controlled TrialCountries of recruitment: ChinaHealth condition(s) or problem(s) studied: hyperlipidemiaIntervention(s): acupuncture and moxibustion, simvastatinStudy type: interventionalDate of first enrollment: December 2014Target sample size: 130Recruitment status: recruiting

## Appendix 1

**Table 2 Tab2:** Major risk factors for CHD other than LDL [13]

Cigarette smoking	
Hypertension (BP ≥140/90 mmHg or on antihypertensive medication)	
Low HDL cholesterol (<40 mg/dL)	
Family history of premature CHD (CHD in male first degree relative <55 years; CHD in female first degree relative <65 years)	
Age (men ≥45 years; women ≥55 years)

**Table 3 Tab3:** CHD and CHD equivalents

• Other clinical forms of atherosclerotic disease (peripheral arterial disease, abdominal aortic aneurysm, and symptomatic carotid artery disease)	
• Diabetes	
• Multiple risk factors that confer a 10-year risk for CHD >20%

**Table 4 Tab4:** Nutrient Composition of the TLC Diet

Nutrient	Recommended Intake
Saturated fat^a^	Less than 7% of total calories
Polyunsaturated fat	Up to 10% of total calories
Monounsaturated fat	Up to 20% of total calories
Total fat	25-35% of total calories
Carbohydrate^b^	50-60% of total calories
Fiber	20-30 g/day
Protein	Approximately 15% of total calories
Cholesterol	Less than 200 mg/day
Total calories (energy)^c^	Balance energy intake and expenditure to maintain desirable body weight/prevent weight gain

^a^Trans fatty acids are another LDL-raising fat that should be kept at a low intake

^b^Carbohydrate should be derived predominantly from foods rich in complex carbohydrates including grains, especially whole grains, fruits, and vegetables

^c^Daily energy expenditure should include at least moderate physical activity (contributing approximately 200 Kcal per day)

**Table 5 Tab5:** Three Categories of Risk that Modify LDL-C Goals

Risk Category	LDL Goal (mg/dL)
CHD and CHD risk equivalents	<100
Multiple (2+) risk factors	<130
0 to 1 risk factor	<160
